#### Medication adjustments

During participation, no adjustments will be made in the Parkinson medication by the research team, and participants are asked to keep their medication stable during the intervention period. However, if medication changes are deemed necessary by the treating neurologist, they are allowed to do so. Any changes in medication will be noted in the patient’s case record form.

### Power and sample size estimate

Our study is powered to show an effect of moderately-high intensive aerobic exercise on the MDS-UPDRS motor score after 6 months. For this, data on the expected effect size of the intervention (change in UPDRS motor score over 6 months with moderately intensive exercise (and standard deviation) compared to controls) is needed. We have performed a pilot study in 21 sedentary PD patients, of whom 11 were randomized to perform moderately intensive aerobic exercise for 6 months. The rest served as controls. The control group had an increase in UPDRS motor score of approximately 6.5 whereas the exercise group increased approximately 1.5 points over 6 months. This results in a difference of 5 points between the groups. The standard deviation of the follow-up measurement was approximately 9.

A clinical important difference for the within-patient change in UPDRS motor score is described in two studies and varies between 2.5-10.8 points [22,23]. Based on a combination of distribution-based and a triple anchor-based approach a minimal effect size was established at 2.5 points change, a moderate effect size at 5.2 points and a large effect size at 10.8 points change in moderately severe PD (H&YI-III) [23]. The influence of disease severity on the clinically important difference remains unclear. However the patient population represented in the MCID studies is similar to our study population, whereas the patients in our pilot where mainly early PD patients. Therefore we assumed a minimal difference between the control and the intervention group at 6 months on the MDS-UPDRS motor score of 3.5 points for the power analysis. Based on an effect size of 3.5 points, a standard deviation of 9 and a two sided α of 0.05, a sample size of n = 105 per group will be needed to obtain a power of 80%.

However, we will perform an ANCOVA analysis in which the baseline measurement will serve as a covariate. As previously described, a correction for the correlation between the baseline and follow-up scores should be made [54]. In our pilot study the correlation (r) was 0.7, resulting in n = 53 patients per group (105 × (1-r^2^)).

Adherence rates in previous moderately-high intensive exercise studies were around 80% [6,55,56]. In our pilot study all patients completed the intervention; however 81.4% of all exercised time was performed within the prescribed intensity. Therefore an attrition rate of between 18-20% was deemed reasonable, resulting in n = 65 patients per group.

### Data collection and management

Prior to data collection, study personnel will review the standard operating procedures (SOP) protocol manual. Assessors will be trained and certified in Good Clinical Practice (GCP) and in performing the MDS-UPDRS according to the guidelines of the Movement Disorder Society. Moreover they will be trained in the other assessments by experienced raters and will rate at least two persons with PD together with an experienced rater. At each measurement interval, data will be collected on paper forms and entered into a web-based data entry portal by the research nurse. Questionnaires are sent by email to the patients and are immediately imported in the electronic database after they are completed. Stored data will be backed up daily. Authenticated investigators will have access to the dataset from any internet access point. Monitoring of the study procedures and progress of the inclusion will be performed by a member of the hospital’s research center, who is not involved in the study. After completion of the study the database will be validated and locked before data-analysis is initiated.

### Statistical analysis plan

The primary and secondary outcomes will all be analyzed with an analysis of covariance (ANCOVA). The dependent variable will be the follow up scores; group allocation, gender and treatment status will serve as fixed factors and the baseline values, age at baseline, Hoehn & Yahr stage, disease duration will serve as covariates. The analyses will be performed on an intention-treat basis. In case of any missing data, sensitivity analysis (last observation carried forward) will be used with delta-adjusting imputation [57]. It should be noted that both an improvement of symptoms in the intervention group and a worsening of symptoms in the control group are considered equally important given the neurodegenerative nature of the disease. In order to determine the optimal effect of aerobic exercise, an additional per protocol analysis will be performed including all patients who completed the program as prescribed.

Adherence to the program will be analyzed according to intention-to-treat, but adherence to the prescribed heart rate will be analyzed per-protocol as this is part of a mediation analysis. Moreover dose-effect relationship will be explored by calculating the correlation between the total exercise volume and the delta score on the different outcomes. An interim analysis will not be performed.

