### Measurements

Assessments will be performed at baseline and after 6 months. All measurements are only performed in *off* state, except for the maximal graded exercise test which is performed in the *on* state and in the UPDRS III, which is performed in both the *off* state (primary outcome) and in the *on* state (secondary outcome). The maximal-graded exercise test is performed in *on* state for two reasons: 1) to minimize any PD related motor limitations, allowing for a maximal cardiovascular performance, and 2) because patients are also instructed to train during their participation in the study in their optimal therapeutic state (*on* state) and the training intensity will be based on the maximal heart rate determined in the maximal graded exercise test. *Off* state is determined as >12 hours after the last Parkinson medication intake (and if applicable: deep brain stimulation switched off during the measurements). Therefore all patients are asked to skip the morning dose of their Parkinson medication at the day of the assessment. All assessments will start at the same time of the day and will be performed in the same sequence, minimizing the difference in time spent in the *off* state between participants. At the end of the assessment, the two aforementioned tests are performed in the *on* state. *On* state is determined by 1 hour after taking a supra-threshold dose of their morning medication (125% of their morning levodopa equivalent dose (LED) for levodopa [19,20]). Half an hour before their lunch, patients are instructed to take this supra-threshold dose to ensure that they reach an *on* state that is equivalent to their everyday functioning, and that persists throughout the *on* state assessments. All tests and questionnaires used are described in Table 2 and are detailed here below.

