## Discussion

Here we present the rationale and design of the Park-in-Shape study, an RCT that aims to provide evidence for the efficacy of aerobic exercise combined with gaming (exergaming) on PD-related symptoms. Previous studies have suggested a positive effect of aerobic exercise on several motor symptoms in PD patients. However, these studies had several shortcomings, as they (a) were either non-randomized/non-controlled or single-blind RCTs, (b) had outcome measures that lacked clinical relevance, (c) had small sample sizes, (d) included other elements besides aerobic exercise, such as resistance or balance training (heterogeneous interventions), or (e) were lab-based, making it difficult to translate the results to everyday life [3,15]. In this regard, strong elements of the Park-in-Shape study include the double-blinded randomized controlled design, the MDS-UPDRS as a valid primary outcome, the large sample size and the unique combination of home-based pure aerobic exercise combined with gaming elements and motivational aspects.

The double-blind character of the Park-in-Shape study is unique and allows for an even distribution of placebo effects in both groups. Obviously, performing an exercise trial in a double blinded fashion is only possible when an active control group is included (which may dilute the contrast with the exercise arm). An advantage to having an active control is that this will likely increase compliance and minimize drop-out rates in the control arm.

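### With only two assessments, last observation carried forward anchors the missing-data analysis on zero change, which the pilot contradicts; no delta is given to correct it

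*Protocol article*

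**What the plan says.** The Statistical analysis plan section specifies ANCOVA on the follow-up score for all primary and secondary outcomes. Group, gender and treatment status are factors; baseline value, age, Hoehn and Yahr stage and disease duration are covariates. On the analysis population it says: "The analyses will be performed on an intention-treat basis". On missing data it has one sentence: "In case of any missing data, sensitivity analysis (last observation carried forward) will be used with delta-adjusting imputation". No delta is given, and no other handling of a missing 6-month score is named.

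The Measurements section says: "Assessments will be performed at baseline and after 6 months". Table 2 shows no outcome visit in between.

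The Power and sample size estimate section reports the pilot: "The control group had an increase in UPDRS motor score of approximately 6.5 whereas the exercise group increased approximately 1.5 points over 6 months". It goes on to allow for attrition of 18–20%. The section on drop-outs and adverse events says that patients who drop out will be encouraged to attend follow-up. The Discussion says of the active control that "this will likely increase compliance and minimize drop-out rates in the control arm".

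**The concern.** Carrying the last observation forward presupposes a series of visits. Here the only earlier value is baseline, so the method becomes baseline carried forward and the imputed change is exactly zero. In a progressive disease, with a pilot in which both arms got worse, zero change is better than the expected course in either arm. The analysis plan itself counts worsening in the control group as part of the treatment contrast. Carrying baseline forward removes that worsening for the patients whose scores are missing.

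A delta shift can correct this, but only if it is about as large as the progression that was not seen. With no delta stated, the natural starting value is 0, which leaves the zero-change rule untouched. At stake is whether the robustness check on an intention-to-treat outcome, with attrition of 18–20% allowed for, can be trusted in either direction.

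**Working it through.** **The plan's own figures.** The inputs are: "Based on an effect size of 3.5 points, a standard deviation of 9 and a two sided α of 0.05", with 80% power.
- Unadjusted: n = 2 × (1.96 + 0.842)² × 9² / 3.5² ≈ 104 per group (stated 105).
- ANCOVA correction: 105 × (1 − 0.7²) = 53.55 (stated 53).
- Attrition: 53 / 0.82 = 64.6, so 65 (stated 65). At 20% attrition, 53 / 0.80 = 66.25, so 67.

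The sample size reproduces closely enough to use 65 per arm, SD 9 and r = 0.7 below.

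**Bias formula.** Let m be the mean 6-month change, d the share without a 6-month score and δ the delta added to the carried-forward baseline, with e for exercise and c for control. The true effect, positive when exercise is better, is m_c − m_e. With scores missing completely at random, the imputed analysis estimates

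[(1 − d_c)m_c + d_c δ_c] − [(1 − d_e)m_e + d_e δ_e],

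so the bias is d_e(m_e − δ_e) − d_c(m_c − δ_c). With δ = 0 this is d_e m_e − d_c m_c.

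**A true effect, δ = 0.**
- Effect 3.5, 20% missing in both arms: 0.80 × 3.5 = 2.8 however the 3.5 is split between arms. Simulated power is about 73–75%, against 78–79% for ANCOVA on observed scores.
- Pilot changes (6.5 and 1.5), 20% missing in both arms: 0.20 × 1.5 − 0.20 × 6.5 = −1.0, so 5.0 becomes 4.0.
- Pilot changes, 20% exercise and 5% control missing: 0.20 × 1.5 − 0.05 × 6.5 = −0.025, almost no bias.
- Effect 3.5 as 6.5 versus 3.0 (assumed), 5% exercise and 20% control missing: 0.05 × 3.0 − 0.20 × 6.5 = −1.15, so 3.5 becomes 2.35. Power is about 55%, against 82% on observed scores.

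**No true effect, 20% exercise and 5% control missing.** Missing rates, common worsening and deltas are all assumed.

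| Worsening in both arms | δ in both arms | Bias favouring exercise | Type I error (simulated) |
|---|---|---|---|
| 6.5 | 0 | 0.15 × 6.5 = 0.975 | about 14% |
| 3.0 | 0 | 0.15 × 3.0 = 0.45 | about 7% |
| 1.5 | 0 | 0.15 × 1.5 = 0.225 | about 5% |
| 6.5 | 3.25 | 0.15 × 3.25 = 0.49 | about 8% |
| 6.5 | 6.5 | 0 | about 5% |

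The error rates come from repeated simulated trials with 65 per arm, SD 9 at both visits, r = 0.7 and ANCOVA on arm and baseline. In the first row, ANCOVA on observed scores holds about 5%. With equal 20% missingness and no effect, there is no bias and the error rate stays at about 5%.

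**The case against.** Four points on the other side have weight.

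First, the sentence couples carrying forward with delta adjustment. A reader might infer that drop-outs are simply assigned zero progression, but a non-zero delta departs from exactly that, and a delta equal to each arm's own progression recovers the true difference. This stands. The criticism is therefore of the anchor and the unstated delta.

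Second, the procedure is labelled a sensitivity analysis. A reader might infer that it is the primary handling, because nothing else is named. The text does not say so, and a fuller plan that is not shown may give both the primary handling and the deltas. This also stands. It limits the consequence but does not make baseline a sound starting point.

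Third, it is tempting to say that bias arises for every drop-out and whenever drop-out differs by arm. Neither is right. Drop-outs are encouraged to return, and only those without a 6-month score are imputed. Equal missingness also dilutes a true effect, while the pilot changes with 20% versus 5% missing give almost none. Unequal missingness is the relevant condition only when there is no effect and patients worsen.

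Fourth, the missing rates by arm are not in the document. The Discussion expects the active control to keep control drop-out low; it does not say lower than in the exercise arm. The app and coaching support both arms, and all pilot patients completed the intervention. At 20% versus 16% missing, even with both arms worsening by 6.5, the bias is only 0.04 × 6.5 = 0.26 points and the type I error stays near 5%.

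**Conclusion.** The concern holds in a limited form and should be fixed. The schedule turns carrying forward into a zero-change anchor that the protocol's own pilot contradicts, and the document gives no delta to move it. At delta 0, equal 20% missingness costs a fifth of a true effect (3.5 becomes 2.8). With no effect, the spurious benefit at 20% versus 5% missing runs from about 0.2 points (type I error about 5%) to about 1.0 point (about 14%), depending on whether both arms are assumed to worsen by 1.5 or 6.5 points. A delta of about half the true progression leaves about 0.5 points and 8% in the latter case; a delta that matches it leaves nothing.

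These sizes rest on assumed missing rates by arm, assumed progression under no effect, SD 9 at both visits and scores missing completely at random. They also treat the planned attrition as missing outcomes, which overstates missingness to the extent that drop-outs return. The documents do not show that the primary result is biased; they show that the stated robustness check starts from a poor place.

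**What to change.** Drop last observation carried forward as the anchor. State as the base analysis the planned ANCOVA on all randomised patients with an observed 6-month score, including drop-outs who return for it, or the equivalent multiple imputation under missing at random given the covariates already listed.

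Keep the planned delta adjustment as the sensitivity analysis, but apply it from that imputation. Vary the deltas by arm over a stated range that covers the pilot's progression, 0 to 6.5 points, and report where the conclusion changes. Imputing missing exercise-arm scores from the control-arm distribution is an optional addition.

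The cost is wording and analysis code, settled before the database is locked. No new data or patients are needed. The sensitivity results may come out slightly less favourable to exercise.

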##### Adherence

Adherence will be determined based on the number of dropouts and the training frequency in both groups, as well as the total time exercised within the prescribed heart rate zone in the intervention group.

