#### Aerobic exercise (intervention group)

The intervention is multifaceted and consists of a unique combination of home-based aerobic exercise, enhanced with virtual reality software and real-life videos, the use of a motivational app and coaching with tele-monitoring from a distance. Aerobic exercise, performed on a stationary home trainer, forms the basis of the intervention. The home trainer is connected to an all-in-one computer equipped with software (Simultrainer Europe Ltd.) that provides visual feedback and virtual coaching (together with the aerobic workout, this combination is referred to as “exergaming”). Patients are instructed to train at least 3 times a week for 30–45 minutes within a predetermined heart rate zone. The heart rate zone is based on the heart rate reserve (HRR), calculated with the Karvonen method; the lower bound will gradually increase from 50% to 70% of the HRR (the upper bound is set at 80%). During the training session, the actual heart rate and time exercised within the heart rate zone, is visualized providing direct feedback. The software offers the opportunity to (a) cycle classical bike routes accompanied by real-life videos of the route, (b) cycle in a virtual world in which they can compete against their own best previous performance or virtual competitors; and (c) to perform an adjusted arcade game that is driven by the patient’s cycling performance. Taken together, this serves to motivate the patients *during* the actual exercise.

In addition, we designed a customized tablet-based motivational app (Park-in-Shape app, designed by IJsfontein Interactive Media Ltd.) to motivate patients both *before* and *after* the actual exercise. Specifically, the app shows exercise goals, provides support, and gives feedback about performance. Patients can view their results in a comprehensible way and can invite supporters to track their progress. Supporters can stimulate them to reach their goals by cheering them on, complimenting them on their performance, and promising incentives when they reach one of their goals.

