Every fortnight a coach will have telephone contact with the participants to check their progress, to adjust their training schedule (if necessary) and to provide support. At least every 4 weeks the training schedules are evaluated and if the patient was easily able to adhere to the prescribed heart rate zone, the heart rate zone is raised. This allows for a graded increase in the aerobic exercise and offers a reward system by setting goals. The coach can decide on the individual intervals of these fitness checks. Communication between the bike computer and the motivational app ensures that adjustments in exercise goals are immediately and correctly enforced. Data from the training sessions are automatically saved after each session and uploaded to a secured server, allowing the coach to track the progress from a distance.

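### Adherence to the heart-rate zone is to be analysed per-protocol, in a set selected on adherence, and the stated reason (mediation) does not support that choice

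*Protocol article*

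**What the plan says.** All places are in the protocol article.

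- **Statistical analysis plan.** Programme adherence is analysed by intention-to-treat. In the same sentence, heart-rate adherence is treated differently: "adherence to the prescribed heart rate will be analyzed per-protocol as this is part of a mediation analysis".
- **Same section, definition of the set.** The per-protocol analysis is described as "including all patients who completed the program as prescribed". No other definition and no numeric threshold are given.
- **Aerobic exercise (intervention group).** The prescription includes the zone: "Patients are instructed to train at least 3 times a week for 30–45 minutes within a predetermined heart rate zone".
- **Adherence.** The heart-rate component is "the total time exercised within the prescribed heart rate zone in the intervention group". Dropouts and training frequency are recorded in both groups.
- **Stretching (active control).** Controls have no aerobic component, and they note only how often they exercised.
- **Statistical analysis plan, dose-effect step.** This is explored by "calculating the correlation between the total exercise volume and the delta score on the different outcomes". No analysis set is named for it.

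**The concern.** Adherence is a listed secondary outcome, and the Discussion says that the trial will show whether the intervention is feasible in real life. For an exercise trial about intensity, time in the zone is the central part of that question. It cannot be answered from patients who were kept because they did what was asked.

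The reason given for the restriction is mediation. A mediation analysis of a randomised effect needs the opposite: the mediator's full range, values in both arms, and the randomised comparison intact. A per-protocol set built on completion supplies none of these for in-zone time.

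The dose-effect step has a related but smaller weakness. It correlates volume with a raw change score, while the main model in the same section adjusts for baseline.

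**Working it through.** **No figure in the plan tests this point.** The sample size rests on the primary ANCOVA and does not use the per-protocol set. It reproduces closely: 104 per group for 3.5 points, SD 9, two-sided 0.05 and 80% power (stated 105); 105 × (1 − 0.7²) = 53.55 (stated 53); 53 / 0.82 = 64.6, so 65 (stated 65).

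**1. Is the set selected on the variable being studied?** The set is those who followed the prescription, and the prescription has three parts: frequency, duration and zone. On the plain reading, the zone helps decide who is analysed. On a narrower reading (sessions completed, whatever the intensity), selection remains. The measure is total time in the zone, which accumulates over sessions, so removing patients who trained too little removes low totals.

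**2. Direction and possible size.** Assume that adherence is normal and that the set keeps the best-adhering share *p* of the 65 aerobic patients. Neither assumption is in the article. With c = Φ⁻¹(1 − p):

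- rise in mean, in SD units: λ = φ(c) / p
- SD ratio: √(1 + cλ − λ²)

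| p kept | patients (of 65) | c | λ | SD ratio |
|---|---|---|---|---|
| 0.90 | about 58 | −1.28 | 0.195 | 0.84 |
| 0.80 | 52 | −0.84 | 0.350 | 0.76 |
| 0.70 | about 46 | −0.52 | 0.497 | 0.70 |
| 0.50 | about 32 | 0 | 0.798 | 0.60 |

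The size depends on the unstated cut-off. The direction does not.

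**3. Can in-zone time mediate the randomised contrast?** It is recorded in one arm. A mediator of the allocation effect must have a value under each allocation; here the control value does not exist.

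**4. What does restriction to completers cost?** Assume that adherence correlates ρ with a prognostic factor, that this factor correlates 0.3 with the outcome, that only the aerobic arm is selected on the zone, and that the true effect is zero. The residual SD is 9 × √(1 − 0.49) = 6.43. The spurious shift is 6.43 × 0.3 × ρ × λ:

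- ρ = 0.2, p = 0.90: 6.43 × 0.3 × 0.2 × 0.195 = 0.08 points
- ρ = 0.5, p = 0.50: 6.43 × 0.3 × 0.5 × 0.798 = 0.77 points

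That is about 2% to 22% of the 3.5-point target.

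**5. Dose-effect step.** With the pilot's r = 0.7 and equal variances at the two visits (assumed), corr(delta, baseline) = −√((1 − r)/2) = −√0.15 = −0.39. If volume is related to the follow-up score only through baseline and correlates −0.3 with baseline severity (assumed), then volume and delta correlate (−0.3) × (−0.387) = +0.12 with no dose effect at all. The sign reverses if the assumed correlation does.

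**The case against.** **Completion and intensity may be separate.** The Power and sample size estimate section reports that every pilot patient completed the intervention although only 81.4% of exercised time was at the prescribed intensity. So the authors can speak of completion without an in-zone threshold, and a cut-off may sit in an analysis plan that is not shown. This stands to the extent that the degree of selection is unknown. It does not remove selection, for the reason in step 1.

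**The mediator is not named.** The article says that heart-rate adherence is part of a mediation analysis. It does not say that in-zone time is the mediator or that the whole mediation analysis is per-protocol. VO2max is scheduled at both visits and may be what is intended. This stands. But then the mediation gives even less reason to restrict the reporting of in-zone time.

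**Stronger readings that the article does not support.**

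- A reader might infer that all adherence is studied only in adherers. It is not: dropouts and training frequency are analysed by intention-to-treat.
- A reader might apply the range restriction to the dose-effect correlation and say that a true correlation would be attenuated by a given amount. That step has no stated per-protocol restriction.
- The zone is a moving target, since "if the patient was easily able to adhere to the prescribed heart rate zone, the heart rate zone is raised", so equal in-zone minutes need not mean equal intensity. The dose-effect step, however, uses total exercise volume, not in-zone time, so this does not count against it directly.

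**The dose-effect step is exploratory.** Volume is not randomised within an arm, and a change score is a recognised choice. This is fair, and it makes the baseline point minor. The +0.12 above would also hide a benefit, not create one.

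**Conclusion.** The point holds for heart-rate adherence only. As written, the plan reports a component of a named secondary outcome in a set selected on adherence. This will tend to overstate in-zone adherence and narrow its range. The pilot's 81.4% was a share of all exercised time, so the trial's per-protocol figure would also not be comparable with it.

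The size cannot be derived from the article. Under the assumed normal distribution with 90% to 50% kept, the mean rises by about 0.2 to 0.8 SD and the SD ratio is 0.84 to 0.60. These figures are illustrations.

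The mediation rationale fails whatever the cut-off, because in-zone time has no control-arm value and selecting completers abandons the randomised comparison. That in-zone time is meant as the mediator is the natural reading, not a stated fact.

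The primary intention-to-treat ANCOVA, programme adherence and the sample size are untouched. This should be corrected, but it does not threaten the main result.

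**What to change.** 1. Report time in the heart-rate zone for all patients randomised to aerobic exercise, including those who stopped early. If a per-protocol description is kept beside it, state the criterion that defines the set.
2. Name the mediator. Run any mediation analysis in all randomised patients with a mediator measured in both arms, adjusted for its baseline value and the baseline outcome. VO2max is already measured at both visits.
3. In the exploratory dose-effect step, regress the 6-month score on exercise volume and the baseline score in place of the volume-delta correlation, and state the analysis set.

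The cost is a change of wording and modest extra analysis. Training data are uploaded automatically after each session, so no new data collection is needed. The real downside is that reported in-zone adherence will be lower.
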